Precision medicine emphasizes the tailoring of disease management to patient characteristics and values to improve patient care and outcomes [10]. Clinical prediction models that objectively turn observed patient characteristics into actionable risk estimates are major enablers of precision medicine [11]. By quantifying the magnitude of risk and treatment benefit, clinical prediction models improve risk communication and informed decision-making between the patient and their care provider, potentially resulting in high satisfaction with, and adherence to, therapies [12]. However, an attractive feature of simple decision tools (e.g., frequent exacerbator definition) in the traditional patient-care provider encounter is that they can be applied without much added burden to the encounter. Historically, ease of use has been a component of clinical “sensibility” of clinical prediction models [13]. The increasing availability of electronic health records (EHR), which enable real-time data retrieval and automated risk calculation, should render the simplicity argument moot.

British Columbia (BC), a Canadian province with a publicly funded healthcare system serving a population of 5.2 million (as of 2021), is amid a major transition to a harmonized EHR platform. The *IM*plementing *P*redictive *A*nalytics towards efficient *C*OPD *T*reatments (IMPACT) study capitalizes on this window of opportunity to integrate a risk prediction model for COPD exacerbations into this EHR system for routine care and evaluate its impact on quality of care and patient outcomes. The risk prediction model of interest, named ACCEPT (*AC*ute *C*OPD *E*xacerbation *P*revention *T*ool) [14, 15], was designed specifically to address the shortcoming of previous studies and is considered the first COPD exacerbation clinical prediction model to be ready for clinical practice implementation [16].

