### Phase 2: A stepped-wedge cluster randomized control trial

#### Study design and setting

To test the effect of the intervention package (ADI and patient tool), we will conduct a prospective stepped-wedge cluster RCT. The unit of randomization will be staff pulmonologists at the two study sites. A stepped-wedge trial design was chosen for multiple reasons. First, clinical prediction model implementation studies should not randomize patients because of potential learning effects (changes in physician behavior after exposure to prediction model, even towards patients in the other group) [28]. Second, the stepped-wedge RCT is an implementation-oriented study design, since by the end of the trial all clusters will be assigned to the intervention arm.

In this trial, pulmonologists (clusters) will be assigned to treatment as usual (comparison arm) at the beginning of the study, with successive assignment to the intervention arm completed in a one-directional, staggered format. The one-way crossover from comparison to intervention will be allocated using a computerized random number generator and completed by the project manager during the first month of the study. Furthermore, due to the nature of the intervention, masking is not possible; thus, blinding will not be applied at the patient or cluster level. However, the allocation sequence will be concealed. Key study design features are shown in Fig. 2.

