#### Study population

Since the intervention will be embedded into the EHR as a standard clinical decision support system and will be part of routine care, all staff pulmonologists at the two study sites (*n* = 28) will participate automatically in the study. However, conservatively anticipating data from the practice of four physicians will not be used for this study for various reasons, such as an extended leave; we aim to use data from 24 pulmonologists, who will comprise the study clusters. Individual patients who are referred to one of the participating pulmonologists at a study site with a physician-assigned diagnosis of COPD will be invited to participate in the clinical trial. For inclusion, individuals must be as follows: (1) a legal Canadian resident, (2) aged 18 years and older, and (3) able to understand English.

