#### Study procedures

##### Recruitment, enrollment, and consent

At the beginning of the study (where all pulmonologists are assigned to the comparison arm), the project manager will review key information from the study protocol with participating pulmonologists. All pulmonologists will be emailed the latest CTS guidelines [6] and will be provided refresher training on the guidelines, if requested. Participation in these orientation interactions, however, will not be mandatory, and lack of participation by a pulmonologist will not exclude them from the study. In addition, before switching a given pulmonologist to the intervention arm, we will provide one-on-one training sessions on the use of the ADI and patient tool. For the ADI training, emphasis will be on how the software operates and how the ADI should be used and interpreted during clinical practice. For the patient tool, the training will include a detailed walk-through of the material, and pulmonologists will have the opportunity to customize the tool according to their practice preference, in a manner that does not affect the validity and consistency of the intervention (e.g., on which monitors they want to see the notifications, how large the fonts should be). A run-in period of 1 month is considered during which training and troubleshooting will take place (Fig. 2). Data gathered during this period will not contribute to the analysis.

Data collected for the purpose of primary endpoint assessment will occur anonymously with a waiver of prior subject consent (Fig. 4). The alignment of prescribed medication with guidelines is directly targeted at measuring the relevant process-of-care variable. The information required to ascertain this endpoint is available through EHR and will be collected as aggregate data for analysis without recording any patient identifiers or changing any aspect of the COPD care being received by the individuals to whom the information relates.

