##### Data collection

The total duration of the trial is 30 months. Initially, all participating pulmonologists will be in the comparison arm. After 6 months, two randomly selected pulmonologists will be reassigned to the intervention arm every other month (Fig. 2). In month 18, the last two pulmonologists will be assigned to the intervention arm, and patient recruitment will continue until month 24. Follow-up data will be collected until month 30 to ensure 6 months of follow-up data for all patients.

To assess the primary endpoint, the prescribed versus recommended treatments will be automatically documented and collected in aggregate form under a unique identification (ID) code assigned to each pulmonologist. If a patient consents to the longitudinal component, a baseline study visit will be conducted that includes administration of questionnaires to collect clinical and patient-reported data to assess secondary outcomes (Fig. 4). Subsequently, two follow-up appointments will be arranged at 3- and 6-month post initial visit via telephone. If a patient sees an enrolled pulmonologist multiple times throughout the 24-month study period, the first visit with the pulmonologist will be used to mark the start of the follow-up period for longitudinal data collection, unless the pulmonologist was reassigned to the intervention arm between visits. In this case, if the patient has consented to the longitudinal component, the follow-up period will be reset during the first visit the pulmonologist is in the intervention arm, and the patient will be followed for another 6 months after the initial intervention arm visit.

To deliver the intervention package, site coordinators will set up automatic software triggers for all eligible patients seeing a pulmonologist allocated to the intervention arm. A trigger will launch when the pulmonologist opens a patient’s EHR chart during the patient encounter, and the ADI will be pre-populated with predictor values. If a predictor value is not retrieved from a patient’s EHR, the empty fields will be highlighted and will be fillable through dictation or by typing directly into the ADI computer interface. At the end of the encounter, the pulmonologist will print the customized patient tool that will be distributed by the research coordinator.

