#### Data analyses

##### Sample size calculations

Details of the sample size calculation is provided in the Supplementary Material — Sect. 2. In summary, the sample size is based on a formula for a stepped-wedged cluster RCT under a cross-sectional sampling method [44, 45], accounting for the variance in inflation due to the intra-cluster correlation and an adjustment for unequal cluster sizes. Sample size calculation was based on a type 1 error of 0.05 and a power of 80%. The current rate of prescription appropriateness was based on our analysis of BC’s administrative health data [46]. The unadjusted sample size was estimated to be 528 per arm.

The design effect is a function of the overall design features (i.e., the cross-over feature, number of clusters, run-in period), as well as the intra-cluster coefficients and cluster autocorrelation. These were obtained from a dedicated analysis of administrative health data from BC using prescription patterns from all physicians in the province [46]. The estimated intra-cluster coefficients and cluster autocorrelation were 0.026 and 0.491, respectively, resulting in a design effect of 2.15. Finally, the design effect was further adjusted for unequal cluster sizes [47], giving rise to a value of 2.18. Based on these, the total sample size is: 528 × 2.18 $$\approx$$ 1153.

To test the feasibility of achieving this sample, we performed an audit of the 2019–2020 fiscal year in one of the study sites and recorded 5559 visits. We estimate 17% of visits are due to COPD and eligible for this study. Given patient traffic in this site is expected to contribute to 60% of the overall traffic, and the 2-year recruitment window, the expected total number of eligible patients will be 3024. Therefore, to achieve the desired sample size, we will need to obtain the primary endpoint for 38% of the visits, a figure that we consider achievable given our experience with clinical studies at both sites.

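### The switching order is described as a random draw of pulmonologists across two sites, with no site restriction stated and no site term named; if unrestricted, site and switch time can be linked by chance, to a small degree

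*Protocol article*

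**What the plan says.** Under Study design and setting, the article states: "The unit of randomization will be staff pulmonologists at the two study sites". In the same section the crossover order is "allocated using a computerized random number generator and completed by the project manager during the first month of the study". Under Data collection, after six months in which every pulmonologist is in the comparison arm, "two randomly selected pulmonologists will be reassigned to the intervention arm every other month", and "In month 18, the last two pulmonologists will be assigned to the intervention arm". Under Study population, four of the 28 staff pulmonologists are expected to yield no usable data: "we aim to use data from 24 pulmonologists, who will comprise the study clusters".

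On the sites themselves, the sample size section says of the audited clinic: "Given patient traffic in this site is expected to contribute to 60% of the overall traffic". The number of pulmonologists at each site is not given.

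The Statistical analyses section plans a generalized linear mixed model with a random effect per pulmonologist, time as a fixed effect, patient covariates and other available covariates. Site is neither named nor excluded. Nowhere does the article say whether the draw is simple, blocked, stratified or otherwise restricted.

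**The concern.** With two sites and 24 clusters, a draw that takes no account of site can put most of one site's pulmonologists early in the sequence and most of the other's late. Site then becomes associated with exposure to the intervention, and two kinds of site effect can leak into the estimate.

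- **A stable difference between sites in prescription appropriateness.** The pulmonologist random effect absorbs this only in part, because the model still draws some information from comparisons between clusters.
- **A change at one site during the trial.** A time effect common to both sites cannot absorb it.

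The second kind is conceivable here. Site coordinators set up the software triggers and a coordinator hands out the patient tool. The intervention and the primary endpoint both run through the electronic record, and the Introduction says the province "is amid a major transition to a harmonized EHR platform". At stake is a chance shift in the primary estimate, fixed once the single draw is made in month 1, which site balance would largely avoid.

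**Working it through.** **Inputs from the article.** 24 clusters; total sample 1153; intra-cluster correlation ρ = 0.026; cluster autocorrelation c = 0.491; 60:40 traffic; 24 months of recruitment; a one-month run-in whose data are dropped ("A run-in period of 1 month is considered during which training and troubleshooting will take place").

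**The article's own figure.** 528 × 2.18 = 1151, against 1153 stated. Since 1153/528 = 2.184, the gap is rounding. The 528 and the design effect of 2.15 cannot be rebuilt, because their details lie in a supplement that is not shown.

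**The stated pace.** Two pulmonologists every other month up to month 18 gives:
- starting in month 6: months 6, 8, …, 18, which is 7 steps and 14 pulmonologists;
- starting in month 8: months 8, 10, …, 18, which is 6 steps and 12 pulmonologists.

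Neither gives 24, so some other pace has to be assumed for the calculation.

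**Assumptions not in the article.** Two switches per month in 12 steps (months 7 to 18); site splits of 12/12, 14/10 and 16/8; outcome SD of 0.5; a linear approximation to the logistic mixed model; site effects of 10 percentage points, chosen for illustration.

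**How far the sites can drift apart.** The chance that a random pair comes from one site is 1 − 144/276 = 48% (12/12) or 1 − 140/276 = 49% (14/10). The chance that all 12 pairs are mixed under 12/12 is 2^12/C(24,12) = 0.15%. Over repeated draws, the difference between sites in mean switch month has an SD of about 1.5 months, and it is 3 months or more in 3 to 7% of draws.

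**Shift in the estimate.** For a pulmonologist with m patients per month, the monthly mean has variance σ²[(1−ρ)/m + ρ] and covariance σ²ρc between months. With Z holding the month effects and the treatment indicator, the treatment estimate is the treatment row of (Z′V⁻¹Z)⁻¹Z′V⁻¹ applied to the outcomes. Applying that row to a site pattern gives the shift in one draw. Its spread over several hundred draws is:

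| 10-point site effect | Unrestricted draw, no site term | Unrestricted draw, site term | Site-balanced sequence |
|---|---|---|---|
| Constant difference | SD about 1.3 | 0 | 0 (12/12, 16/8); about 0.1 (14/10) |
| Change at one site at month 12 | SD about 0.8–0.9 | SD about 0.5 | about 0 (12/12); about 0.1 (14/10) |
| Linear drift at one site | SD about 0.7 | SD about 0.13 | about 0 to 0.1 |

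Without restriction, the 95th percentile of the absolute shift is about 2.5 points for the constant difference and 1.7 for the one-site change. If pulmonologists are instead fitted as fixed effects, the constant difference drops out, and the one-site change has an SD of about 0.7 (95th percentile about 1.3). In every case the shift averages zero apart from simulation noise.

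**Against the trial's own uncertainty.** The standard error is about 0.1155 × 0.5 = 5.8 points (5.9 in some variants). The largest SD above is 1.3/5.8 = 0.22 of it. Adding it in quadrature multiplies the total spread by √(1 + 0.22²) = 1.02.

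**Cost of the remedies.** Site balance leaves the standard error unchanged. A site term after an unrestricted draw raises it from 0.1155 to 0.1160 per unit SD, about 0.4%.

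**Losses after the draw.** With balanced sequences for 28 pulmonologists and four lost at random (assumed splits 14/14, 16/12, 17/11), the one-site change leaves an SD of about 0.27, against 0.59 to 0.68 unrestricted.

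**The case against.** The strongest reply is that the article never says the draw ignores site. A random number generator and randomly selected pairs are both compatible with a stratified sequence, and a condensed article may leave the restriction and the covariate list to the full protocol. This stands: a reader might infer that simple randomisation is used, but the text does not say so. The point is therefore conditional on the draw being unrestricted.

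A reader might also infer that the sites are unequal in pulmonologists, that a one-site disruption from the record-system transition is expected, or that the primary estimate will be biased. None of these is supported. Inequality is documented for patient traffic only. The Discussion says harmonized record systems had recently been implemented in both clinics, which weakens the transition argument, and no change at a single site is forecast. The primary endpoint is documented automatically, so coordinators' shortlisting of patients bears on the consented longitudinal component. The shift averages zero over the randomisation and is small beside the standard error.

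Finally, a site term alone might seem to make stratification unnecessary. It fully removes a constant difference and most of a linear drift, but about 0.5 points of SD remain for an abrupt one-site change. Site balance brings that to about zero with equal sites and no losses, so the two remedies are complementary.

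**Conclusion.** The point holds as a minor, conditional one. The article states no site restriction on the switching order and names no site term. If neither exists, a 10-point site effect moves the estimate by chance with an SD of about 0.7 to 1.3 points, depending on its form and on how pulmonologists are modelled. That is at most about 0.22 of a standard error of 5.8 to 5.9 points. For comparison, the average improvement the article cites for decision support tools is 5.8%.

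These sizes rest on the assumed 10-point effects, the site splits, the monthly pace, the outcome SD of 0.5 and the linear approximation. It would be too strong to say that stratification abolishes the problem: with a 14/10 split one pulmonologist per site cannot fill every step, and pulmonologists lost after the draw disturb the balance. The mismatch between the stated pace and 24 clusters needs no such assumptions.

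**What to change.** 1. Reconcile the number of pulmonologists, the number switching per step, the interval between steps, and the first and last switch months. No sequence for 24 can be drawn from the schedule as stated.
2. State whether the sequence is restricted by site. If it is not, order the pulmonologists at random within each site and fill the steps in the sites' ratio (one from each site where numbers are equal).
3. Name site as a fixed effect in the mixed model.

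The whole order is drawn once, in month 1, so this means a small change to the randomisation program and one model term, with no extra patients, staff or time. The standard error rises by about 0.4% if only the site term is added, and hardly at all once the sequence is balanced. The order becomes slightly more predictable within a site, which matters little because all pulmonologists take part automatically and are unblinded.

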##### Data monitoring and management

Before trial initiation, we will establish a Data Safety and Monitoring Committee (DSMC) to ensure that the rights and overall well-being of participants are safeguarded and attend to any immediate safety matters. Members of the DSMC will be selected by the study investigators but will act fully independently from the study, its investigators, and the funder. The DSMC will consist of individuals with methodological and clinical expertise.

Throughout the trial, study personnel will be available to troubleshoot and address questions about ADI use and triggers. Biweekly reports will be generated to track the frequency of ADI triggering, ADI completion, and proportion of recommendations overridden. This will allow us to determine the fidelity of ADI usage. If use of the ADI is lower than expected for a pulmonologist, we will approach them to determine potential issues.

All research data will be entered daily by the clinical research coordinators at each study site. We will use an electronic case report form for direct data entry into REDCap®. This minimizes data entry errors and improves data quality through the immediate application of data validation rules and boundary checking. Each record will be assigned a unique subject ID that will not include any personal or identifying information. A master list linking identifiable participants to research data will be kept encrypted and password protected under the secure storage system, and only the principal investigators will have access to the master list. Study statisticians and investigators will only have access to anonymized research data.

##### Process evaluation

The success of clinical decision support relies on an uptake of the tools into practice. To optimize uptake, it is critical to determine how the tools are being used by the patient-pulmonologist dyad. A sampled subgroup of patients (*n* = 20) and all pulmonologists (*n* = 24) will be invited for the qualitative process evaluation aiming to further improve risk communication and clinical workflow. Patients will be selected based their BMQ-COPD scores to ensure maximum variation in representation. After the patients complete a brief demographic questionnaire, we will conduct 1 h, semi-structured, telephone interviews to explore differences in patient experiences, assist with interpretation of trial findings, and provide direction for any further refinements to the intervention.

To gain insight into pulmonologist’s satisfaction, we will use normalization process theory (NPT) to better understand the factors that affected their implementation, with particular attention to clinical burnout and alert fatigue [43]. The 16-item NPT questionnaire covers questions in four important domains: sense-making, participation, action, and monitoring [43]. The information gained will be fed back to the design of the tools before largescale implementation.

#### Data analyses

##### Sample size calculations

Details of the sample size calculation is provided in the Supplementary Material — Sect. 2. In summary, the sample size is based on a formula for a stepped-wedged cluster RCT under a cross-sectional sampling method [44, 45], accounting for the variance in inflation due to the intra-cluster correlation and an adjustment for unequal cluster sizes. Sample size calculation was based on a type 1 error of 0.05 and a power of 80%. The current rate of prescription appropriateness was based on our analysis of BC’s administrative health data [46]. The unadjusted sample size was estimated to be 528 per arm.

The design effect is a function of the overall design features (i.e., the cross-over feature, number of clusters, run-in period), as well as the intra-cluster coefficients and cluster autocorrelation. These were obtained from a dedicated analysis of administrative health data from BC using prescription patterns from all physicians in the province [46]. The estimated intra-cluster coefficients and cluster autocorrelation were 0.026 and 0.491, respectively, resulting in a design effect of 2.15. Finally, the design effect was further adjusted for unequal cluster sizes [47], giving rise to a value of 2.18. Based on these, the total sample size is: 528 × 2.18 $$\approx$$ 1153.

To test the feasibility of achieving this sample, we performed an audit of the 2019–2020 fiscal year in one of the study sites and recorded 5559 visits. We estimate 17% of visits are due to COPD and eligible for this study. Given patient traffic in this site is expected to contribute to 60% of the overall traffic, and the 2-year recruitment window, the expected total number of eligible patients will be 3024. Therefore, to achieve the desired sample size, we will need to obtain the primary endpoint for 38% of the visits, a figure that we consider achievable given our experience with clinical studies at both sites.

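### The sample size section gives 528 as a per-arm number but multiplies it once by the design effect and calls the product the trial total, so one of the two statements is wrong

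*Protocol article*

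**What the plan says.** All of this is in the protocol article, under Sample size calculations. The calculation uses a type 1 error of 0.05 and 80% power. The starting point is "The unadjusted sample size was estimated to be 528 per arm". The intra-cluster correlation and cluster autocorrelation follow: "The estimated intra-cluster coefficients and cluster autocorrelation were 0.026 and 0.491, respectively, resulting in a design effect of 2.15". An adjustment for unequal cluster sizes raises the design effect to 2.18. The section then concludes that "the total sample size is: 528 × 2.18", about 1153.

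For feasibility, the section takes 5559 audited visits at one site in one year, of which 17% are judged eligible. It says that this site accounts for 60% of overall traffic, applies a two-year window, and states that "the expected total number of eligible patients will be 3024". From that it derives that "we will need to obtain the primary endpoint for 38% of the visits".

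The figures behind 528 are not in the article. On the control rate it says only "The current rate of prescription appropriateness was based on our analysis of" provincial administrative data, and it refers the reader onward: "Details of the sample size calculation is provided in the Supplementary Material", Sect. 2, which is not at hand.

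**The concern.** A stepped-wedge design effect of this kind inflates the total number of observations that an individually randomised trial would need. If 528 is needed in each arm, that total is 1056, and 1056 is what should be multiplied by 2.18. The section multiplies 528 and calls the result the total.

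The stated power for the primary outcome, the recruitment target and the judgement that recruitment is achievable all rest on this one product. The limitations paragraph of the Discussion says that the trial is powered for the primary outcome, and this section is the only support the article gives for that. As printed, a reader cannot tell whether 1153 observations give 80% power or about 51%.

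**Working it through.** **Inputs, all from Sample size calculations:** alpha 0.05 (sidedness not stated), power 80%, unadjusted size 528 per arm, final design effect 2.18, stated total 1153, stated eligible pool 3024, stated share 38%.

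**1. Reproducing the stated total.** 528 × 2.18 = 1151. The printed 1153 corresponds to an unrounded design effect of 1153 / 528 = 2.184. The figure therefore reproduces only if 528 is multiplied once.

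**2. Is 1153 the whole-trial total?** 1153 / 3024 = 38.1%, the printed share of all eligible visits. So yes.

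**3. The total if 'per arm' is right.** 2 × 528 = 1056, and 1056 × 2.18 = 2302. The stated 1153 is 50% of this.

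**4. Power at 1153 if 'per arm' is right.** The effective size is 1153 / 2.18 = about 529, or about 264 per arm where 528 is needed. With half the required information:
- two-sided alpha: Φ((1.960 + 0.842)/√2 − 1.960) = Φ(0.021) = 50.8%
- one-sided alpha: Φ((1.645 + 0.842)/√2 − 1.645) = Φ(0.113) = 54.5%

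This needs neither the control rate nor the effect. As a check, illustrative pairs of proportions that need about 528 per arm (for example 27% against 35%, or 54% against 62.5%) give 50.6% to 51.1% power at 264 per arm.

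**5. Is the factor of two already inside the design effect?** If 2.15 converted a per-arm number into a trial total, the total-to-total design effect would be 2.15 / 2 = about 1.08. A generalised least squares variance with correlation 0.026, autocorrelation 0.491 and N = 1153 was computed for eight assumed layouts, seven with 24 clusters and one with 14. It gave total-to-total design effects from 2.02 to 3.83, none near 1.08. The layout figure is not shown, so these layouts are assumptions. They show that the factor of two is not hidden; they do not confirm 2.15 itself.

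**6. Does 2.18 carry over to a larger trial?** No. The design effect rises with the number of observations per cluster-period. With 24 clusters and 12 steps over 13 equal periods (assumed), it goes from 2.02 at N = 1153 to 2.33 at N = 2302 without a run-in, and from 2.27 to 2.64 with one. Solving for N in these two layouts with 1056 as the base gives 2505 and 2977. So 2302 is a lower figure with the design effect held fixed, not a firm requirement.

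**7. Feasibility.**
- Eligible visits at the audited site: 5559 × 0.17 = 945 per year.
- If that site is 60% of all traffic: 945 / 0.60 × 2 years = 3150.
- The printed 3024 equals 945 × 1.6 × 2, which treats the second site as adding 60% of the first site's traffic.
- Share needed for 1153: 38.1% of 3024, or 36.6% of 3150.
- Share needed for 2302: 76.1% of 3024, or 73.1% of 3150.

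The audit counts visits, the pool is then labelled patients, and the required share is again expressed in visits.

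**The case against.** The strongest reply is that 'per arm' may be a slip of two words in a condensed article. If 528 is the unadjusted two-arm total (264 per arm), then 1153 is right and power is 80%. This cannot be ruled out, because the control rate and target effect are in a supplement that is not shown. At mid-range proportions, 528 per arm corresponds to a difference of about 8 percentage points (27% against 35%) and 264 per arm to about 12 (35% against 47%), and nothing in the article selects between them. A reader might infer that the trial is in fact planned at half its required size with 51% power. The documents do not support that as a fact, only as one of two branches. What remains is that the two statements conflict and nothing in the article reconciles them. This is a contradiction in print, not detail left to the supplement.

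A reader might also take the design effect of about 2.0 to 2.3 in the equal-period layouts as confirmation of the stated 2.15. It is not: monthly layouts closer to the timetable under Data collection give values above 3.

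The mismatch of 3150 against 3024 is about 4% and, taken alone, slightly favours the plan. One could also shrink the pool for the four physicians whose data may go unused and for run-in months. For example, 3150 × 24/28 × 23/24 = 2588 would make the share 45% for 1153 or 89% for 2302. That assumes visits fall in proportion, and Study population presents the four physicians as a conservative allowance, not a known loss. These shares illustrate the sensitivity and are not findings.

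**Conclusion.** The section contradicts itself, and one printed statement must change. There are two cases:

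- **528 is the two-arm total.** 1153 and 80% power stand, and the words 'per arm' are wrong.
- **528 is per arm.** 1153 is about half of what the stated inputs require. The total is at least about 2302 with the design effect held at 2.18, and more if it is recomputed at the larger cluster-period size. Power at 1153 is about 51% with two-sided alpha (about 54.5% one-sided) at a design effect of 2.18. The share needed is about 76% of the stated pool, and the judgement that 38% is achievable does not extend to that.

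The article does not settle which case applies. Separately, the eligible pool does not follow from its own inputs: they give 3150 visits, not 3024 patients. That error is small and secondary.

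**What to change.** Check 528 against the underlying calculation in Supplementary Material Sect. 2.

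- If it is the two-arm total, delete 'per arm'.
- If it is per arm, either keep 1153 and restate its power (about 51% at a design effect of 2.18), or restate the total with the design effect recomputed at the new size. Printing 2302 with 2.18 carried over would be inconsistent. Update the required share of visits to match.

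In either case, state whether alpha is one- or two-sided. Correct the pool to 3150, or say that the second site adds 60% of the first site's traffic if that is what was meant. Count visits throughout, and show any deduction for unused physicians or run-in months as a labelled assumption.

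The check is quick and the first outcome costs two words. The second costs either a less favourable power statement or a larger target with a more demanding feasibility figure.
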